# Reduced fetal movement intervention Trial-2 (ReMIT-2): protocol for a pilot randomised controlled trial of standard care informed by the result of a placental growth factor (PlGF) blood test versus standard care alone in women presenting with reduced fetal movement at or after 36^+ 0^ weeks gestation

**DOI:** 10.1186/s13063-018-2859-1

**Published:** 2018-10-01

**Keywords:** Reduced fetal movement, Placental biomarker, sFlt-1/PlGF ratio, Placenta, Maternal serum, Stillbirth, Perinatal mortality, Feasibility

## Abstract

**Background:**

Forty percent of babies who are stillborn born die after 36 weeks gestation and have no lethal structural abnormality. Maternal perception of reduced fetal movement (RFM) is associated with stillbirth and is related to abnormal placental structure and function. The ultimate objective of this trial is to assess whether for women with RFM, intervention directed by measurement of placental biochemical factors in addition to standard care improves pregnancy outcome compared with standard care alone. This is the protocol for a pilot trial to determine the feasibility of a definitive trial and also provide proof of concept that informing care by measurement of placental factors improves neonatal outcomes.

**Methods:**

ReMIT-2 is a multicentre, pilot randomised controlled trial of care informed by results of an additional placental factor blood test versus standard care alone for women presenting with RFM at or after 36^+ 0^ weeks gestation. Participants will be randomised 1:1 to the intervention arm where the blood test result is revealed and acted on, or to the control arm where the blood sample is not tested immediately and therefore the result cannot be acted on. All participants will be followed up six weeks after delivery to assess their health status and views of the trial, along with healthcare costs. A sub-group will be interviewed within 16 weeks after delivery to further explore their views of the trial. Outcomes to determine feasibility of a definitive trial include number of potentially eligible women, proportion lost to follow-up, clinical characteristics at randomisation, reasons for non-recruitment, compliance with the trial intervention and views of participants and clinicians about the trial. Proof of concept outcomes include: rates of induction of labour; Caesarean birth; and a composite neonatal outcome of stillbirths and deaths before discharge, 5-min Apgar score < 7, umbilical artery pH < 7.05 and admission to neonatal unit for > 48 h.

**Discussion:**

Results from this pilot trial will help determine whether a large definitive trial is feasible. Such a study would provide evidence to guide management of women with RFM and reduce stillbirths.

**Trial registration:**

ISRCTN Registry, ISRCTN12067514. Registered on 8 September 2017.

**Electronic supplementary material:**

The online version of this article (10.1186/s13063-018-2859-1) contains supplementary material, which is available to authorized users.

## Background

In the UK, approximately 1 in 220 babies are stillborn, which describes a baby born with no signs of life after 24 weeks of pregnancy [1]. The rate of stillbirth in the UK ranks 24th out of 49 high-income countries and the annual rate of reduction (ARR) is much lower than other comparable nations; for example, from 2000 to 2015, the ARR in the UK was 1.4% compared with 6.8% in the Netherlands [2]. Forty percent of babies who are stillborn die after 36 weeks of pregnancy and have no lethal structural abnormality [3]. If these babies could be identified and delivered earlier, lives could be saved with minimal impact on neonatal services. As well as the loss of life for the child, stillbirth is associated with significant psychological and social consequences for parents and the maternity staff who care for them, along with an economic impact on healthcare services [4]. Thus, a reduction in stillbirth has the potential to save NHS resources and reduce resultant financial costs. One means to reduce stillbirth is to focus on improving care for women at increased risk.

An association between maternal perception of reduced fetal movement (RFM) and stillbirth has been documented for > 40 years [5, 6]. Suboptimal management of RFM has been highlighted in two Confidential Enquiries of antepartum stillbirths carried out in the UK almost 20 years apart [7, 8]. Although there has been national guidance for the management of RFM since 2011 [9], there is significant variation in clinical practice between practitioners and maternity units, with a significant proportion of women not receiving evidence-based care [10–12]. This may, in part, be due to the lack of high-quality evidence to direct the management of RFM in late pregnancy [13]. This manuscript describes the protocol for pilot randomised controlled trial of management of RFM informed by a biochemical test; the protocol has been reported in accordance with the SPIRIT checklist (Additional file 1).

### Rationale for study population

Maternal perception of RFM is associated with increased risk of stillbirth, fetal growth restriction (FGR), fetomaternal haemorrhage and neurodevelopmental delay [14]. RFM is thought to be a symptom of nutrient and/or oxygen restriction [15]. This is supported by observed changes in placental structure and function compared to women with normal fetal activity and the observation that babies born following maternal perception of RFM are relatively acidaemic compared to those with normal fetal movements [16, 17]. Most studies estimate that RFM increases the risk of stillbirth by two- to threefold [14, 18]. Importantly, RFM is a common reason to present to maternity services in the third trimester of pregnancy with 6–15% of women presenting on at least one occasion [19, 20]. Therefore, this trial focuses on women with RFM as a frequently occurring symptom in late pregnancy, which identifies a group of women at increased risk of adverse outcome late in pregnancy.

The need for studies in this area was highlighted by the paucity of evidence identified in a systematic review of the management of RFM [13] and the Stillbirth Priority Setting Partnership, which identified two relevant priorities [21]: (1) which investigations identify a fetus at risk of stillbirth after a mother has experienced RFM; and (2) how can the structure and function of the placenta be assessed during pregnancy to detect potential problems and reduce the risk of stillbirth?

Although RFM is associated with increased perinatal morbidity and mortality, intervention by delivering infants before 36 weeks gestation may increase perinatal mortality as the neonatal mortality rate for singleton pregnancies exceeds the stillbirth rate until 36 weeks gestation and there is evidence of increased morbidity for births before 38 weeks gestation [22]. Therefore, this trial will examine the potential benefit of assessing placental dysfunction using a novel marker of placental structure and/or function in combination with delivery when indicated by that marker at or after 36 weeks gestation.

### Rationale for study design

This is a multicentre pilot trial to determine whether a larger definitive trial of a placental biomarker to inform the decision of whether or not to deliver a baby is possible and provides evidence of proof of concept by assessment of a composite measure of perinatal outcome. The trial design was informed by a single-centre feasibility study (ReMIT study, ISRCTN 07944306) which randomised 120 women to management based on cardiotocography (CTG), ultrasound scan and measurement of human placental lactogen (hPL) versus standard care (CTG and ultrasound if indicated) [23]. This study found that trial participation was associated with a decrease in maternal anxiety and high levels of participant satisfaction confirmed by a minimal loss to follow-up (< 2%). Although the intervention was associated with an increase in induction of labour for RFM, it was not associated with an increased rate of instrumental vaginal deliveries or Caesarean section. There was a reduction in the composite adverse perinatal outcome (perinatal mortality, birthweight < 10th centile, admission to neonatal intensive care unit [NICU], umbilical artery pH < 7.1) from 29% in controls to 12% in the intervention group. These encouraging data indicate that a larger trial is needed to evaluate the potential for this intervention to reduce stillbirth. However, to address stillbirth or perinatal death as a primary outcome would require a very large clinical trial. Assuming a rate of stillbirth of 0.3% in women with RFM, > 82,000 women would be required to detect a reduction in stillbirth of one-third (i.e. to 0.2%) with 80% power and 110,000 with 90% power.

One alternative would be to address whether the intervention prevents significant perinatal asphyxia detected by perinatal death or fetal acidaemia at birth or admission to the NICU for > 48 h. Similar approaches have recently been employed by the INFANT [24] and DIGITAT studies [25]. In the ReMIT feasibility study, this composite outcome had a frequency of 6% [23]. To detect a 30% reduction to 4.2% would require 5000 women with 80% power and 6500 women with 90% power. Such recruitment may be possible using 30–40 sites over 24 months. To determine whether this is feasible, the ReMIT-2 pilot trial will be conducted at approximately six sites over nine months with an aim to recruit 175–225 eligible participants during this time. The sites will vary in size (in terms of number of births per year) to ensure that the data are representative of the range of sites that would participate in the main trial. ReMIT-2 will use the same composite primary outcome measure as for the DIGITAT study. This pilot trial has not been powered to detect a difference in this composite perinatal outcome, but the individual components will be measured to assess proof of concept.

In addition to assessing whether incorporating measurement of a placental biomarker into the management of RFM improves pregnancy outcome, information will also be collected regarding participant and staff experiences of the intervention through qualitative and quantitative measures. These data will provide important information regarding the feasibility and acceptability of the intervention and will help to identify potential barriers, particularly in relation to conducting a larger trial. The economic evaluation will consider the resources required to implement the evaluation, including healthcare costs and the costs to families. The cost-effectiveness of the intervention will be calculated.

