PlGF is bound in maternal blood by soluble-fms-like tyrosine kinase 1 (sFlt-1); therefore, assays to quantify PlGF measure either unbound PlGF or the ratio of sFlt-1 to PlGF. Comparison of these assays revealed no difference in their diagnostic performance [33]. The sFlt-1/PlGF ratio will be used in ReMIT-2 as it is a commonly available test in hospitals in the UK. An sFlt-1/PlGF ratio of ≥ 38 will be used as the threshold to identify significant placental dysfunction as this level increases the likelihood of delivery in women with suspected pre-eclampsia due to intervention to prevent maternal or fetal complications [34]. Before undertaking ReMIT-2, a diagnostic test accuracy study in 318 women presenting with RFM found that an sFlt-1/PlGF ratio of ≥ 38 had a sensitivity of 0.20 and a specificity of 0.88 to identify a composite adverse perinatal outcome (perinatal death, birthweight < 5th centile, umbilical cord pH < 7.1, admission to NICU for > 48 h; unpublished data). This compared to other methods employed, including oligohydramnios (sensitivity 0.12, specificity 0.85) or umbilical artery Pulsatility Index > 95th centile (sensitivity 0.05, specificity 0.95) and potentially represents a modest improvement in prognostic accuracy over ultrasound scan alone.

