### Trial intervention

All participants will have a blood sample taken to measure the sFlt-1/PlGF ratio and will be randomised 1:1 to standard care with the blood sample tested locally at the time and the results revealed and acted on (intervention arm), or for the blood sample to be tested at a later time by a central NHS laboratory so the result is not available to site staff or the participant and therefore cannot be acted on (control arm; Fig. 1). Participants in the intervention arm with an sFlt-1/PlGF ratio ≥ 38 will be offered delivery at 37^+ 0^ weeks (or as soon as possible after 37 weeks) by the most appropriate method and induction of labour should commence within 48 h of this offer. Those in the intervention arm with an sFlt-1/PlGF ratio < 38 or those in the control arm will continue with usual care [9]. Participants in both arms will be free to decline the recommended management plan and may return for any further episodes of RFM before delivery but cannot be re-randomised into the trial.

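### The definitive trial is sized on a 30% reduction, but the protocol's own sensitivity of 0.20 for the chosen threshold, if it carries over, allows at most about 20%

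*Protocol article*

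**What the plan says.** Under Rationale for study design, the protocol proposes a composite of perinatal death, fetal acidaemia or NICU admission beyond 48 h for the definitive trial. It gives that composite a frequency of 6% in the earlier feasibility study and states: "To detect a 30% reduction to 4.2% would require 5000 women with 80% power and 6500 women with 90% power". It suggests that 30–40 sites over 24 months might deliver this, and presents the pilot as the way to find out.

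Under Justification for choice of intervention and placental biomarker, a study of 318 women with reduced fetal movement found that a ratio of at least 38 "had a sensitivity of 0.20 and a specificity of 0.88 to identify a composite adverse perinatal outcome". That composite comprised perinatal death, birthweight below the 5th centile, cord pH below 7.1 and NICU admission beyond 48 h. The data are unpublished and no confidence interval is given.

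Under Trial intervention, intervention-arm women with a ratio below 38 "or those in the control arm will continue with usual care". Only those at or above 38 are offered something different.

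The Abstract (Methods) describes the trial's own measure as "a composite neonatal outcome of stillbirths and deaths before discharge, 5-min Apgar score" below 7, umbilical artery pH below 7.05 and neonatal-unit admission beyond 48 h. This has a component that the outcome behind the 6% lacks.

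**The concern.** In a test-and-treat design, the result can change outcomes only through the women whose care it changes. Events among test-negative women occur under the same care as in controls, so the relative reduction in the whole arm cannot exceed the share of events that fall among test-positive women, which is the sensitivity. A sensitivity of 0.20 and a target of 30% do not fit together, and the protocol never links the two.

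This matters because 5000–6500 is the recruitment against which feasibility is to be considered. If the attainable effect is nearer 20% or below, the pilot could support a main trial that needs at least about twice as many women.

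**Working it through.** **Inputs.** Control rate 6%, target 4.2%, sizes 5000 and 6500 (Rationale for study design). Sensitivity 0.20 (Justification for choice of intervention and placental biomarker). Usual care below 38 (Trial intervention). Allocation 1:1 is stated for the pilot and assumed for the main trial. Two-sided α = 0.05 and no dropout are assumed, as neither is stated beside the figures.

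**Formulas.** With d = p1 − p2 and p̄ their mean, the size per arm is

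n = [1.960·√(2p̄(1−p̄)) + z_β·√(p1(1−p1) + p2(1−p2))]² / d²,

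and with continuity correction n_c = (n/4)·[1 + √(1 + 4/(n·d))]². Power at n per arm is Φ{[d√n − 1.960·√(2p̄(1−p̄))] / √(p1(1−p1) + p2(1−p2))}.

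**Step 1: the protocol's own figures.** For 6.0% versus 4.2% at 80% power, n = (1.960 × 0.3111 + 0.842 × 0.3109)² / 0.018² = 2344 per arm, or 4688 in total. With continuity correction the total is 4908. At 90% power the totals are 6276 and 6496. The corrected values match 5000 and 6500.

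**Step 2: the limit.** Relative reduction = sensitivity × share of flagged events prevented × uptake. With the last two set to 1, it is 0.20, and 6.0% × (1 − 0.20) = 4.8%. A 30% reduction needs a sensitivity of at least 0.30 with both other factors at 1.

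**Step 3: consequences.** At 6.0% versus 4.8% and 2500 per arm, power = Φ[(0.012 × 50 − 0.6265) / 0.3195] = Φ(−0.083) = 46.7%. The table gives sizes without and with continuity correction.

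| Flagged events prevented (full uptake) | Rate | Power, 5000 | Power, 6500 | Total N, 80% | Total N, 90% |
|---|---|---|---|---|---|
| All | 4.8% | 47% | 57% | 11,136–11,468 | 14,906–15,238 |
| Three quarters | 5.1% | 28% | 35% | 20,316–20,758 | 27,196–27,640 |
| Half | 5.4% | 15% | 18% | 46,874–47,540 | 62,750–63,416 |

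**Step 4: recruitment.** Thirty to 40 sites over 24 months is 720–960 site-months. For 5000 women this means 5.2–6.9 per site per month. For 11,136–11,468 it means about 12–16. The pilot's own target, 175–225 over six sites and nine months (54 site-months), is 3.2–4.2.

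**Step 5: the more favourable figure.** The protocol also reports sensitivity rising from 9% to 38% (95% CI 21–57%) when PlGF is added to ultrasound, not for this threshold. The gain is 29 points of all events. The trial, however, randomises women only after CTG and ultrasound are normal. If the ultrasound-detected 9% are nested in the 38% and leave before randomisation, the relevant share is 29/91 = 32%. At 29% a 30% reduction is just out of reach. At 32% it needs 0.30/0.319 = 94% of flagged events prevented, with full uptake.

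**The case against.** A reader might infer that 5000 and 6500 lack their stated power. They do not. The statement is conditional on a fall to 4.2%, and both figures reproduce.

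A reader might also infer that 30% is impossible. The documents do not support that either. The 0.20 is an unpublished point estimate without an interval, on a composite that includes low birthweight and a different pH cut-off; its value for the planned composite could be lower or higher. Assuming that 6–20% of the 318 women had the outcome (19–64 cases), exact 95% intervals run from about 0.06–0.46 to about 0.11–0.32, so 0.30 is not excluded. Even at 0.30, though, every flagged event would have to be prevented.

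Two other figures could be cited for the 30%:

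- The feasibility study's composite fell from 29% to 12%, a relative reduction of 17/29 = 59%. That was a single-centre study of 120 women with a different marker (hPL), a composite including birthweight below the 10th centile, and a different ultrasound policy. It is weak support for this test at this threshold.
- PlGF had a sensitivity of 0.88 for stillbirth. At 0.3%, stillbirth is about 5% of a 6% composite, and 0.05 × 0.88 + 0.95 × 0.20 = 0.23.

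Finally, the pilot is expressly not powered on this outcome, its size rests on margins of error, and no numerical go/no-go rule is stated. It also collects compliance, the composite and control-arm test performance, which are the inputs for re-planning. All of that stands and limits the consequence to the planning yardstick. It does not explain where the 30% comes from.

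**Conclusion.** The point holds as an unreconciled planning assumption. The arithmetic behind 5000 and 6500 is sound; the effect put into it exceeds the roughly 20% implied by the only sensitivity the protocol gives for the test and threshold it uses. At that 20% the main trial would need about 11,100–11,500 women for 80% power or 14,900–15,200 for 90%. If half of flagged events are prevented, it would need about 47,000 and 63,000.

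This rests on four assumptions: the 0.20 carries over to the planned composite, test-negative women receive the same care as controls, the control rate is 6%, and the test is two-sided at 5% with 1:1 allocation. Uptake below 100% lowers the effect further, and participants are free to decline.

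A smaller, separate mismatch is that the 6% belongs to the three-part outcome, while the trial's composite adds a low 5-minute Apgar score. That addition can only hold or raise the base rate, which for a given relative reduction would lower the required size. The protocol gives no figure from which to quantify it.

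**What to change.** In Rationale for study design:

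1. Derive the target effect as sensitivity × share of flagged events preventable × uptake, with a stated source or range for each factor. Say plainly that the 0.20 comes from a different composite and has no interval. If 30% is kept, justify it against that product.
2. Give the main-trial size over the resulting range, including the 20% case, with α, sidedness and allocation stated.
3. Judge recruitment feasibility against that range as well as 5000–6500.
4. State that the 6% is for death, acidaemia or NICU stay beyond 48 h and does not include the Apgar component. Do not simply replace it with a rate pooled over both pilot arms: about 200 women at 6% yields 12 events and a 95% interval of roughly 3.1–10.2%, and pooling would mix any treatment effect into the control rate.

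The cost is recalculation and wording. The main-trial figures become less favourable; pilot enrolment does not change.

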### Sample size and recruitment

As this is a feasibility trial, a formal sample size for estimating between-group effects is not appropriate. ReMIT-2 will recruit over a period of nine months from approximately six UK sites and it is expected that 175–225 participants will be recruited during this time. This number will give estimated margins of error (half width of 95% CI) for the proportion recruited of approximately 5% and for the proportion lost to follow-up after discharge of approximately 7.5%.

The maximum length of time from enrolment to delivery is six weeks. For participants not involved in the Midwife-Led Interview, the follow-up period from delivery to completion of the participant questionnaires is ~ 10 weeks. For the sub-group of participants involved in the Midwife-Led Interview, the follow-up period from delivery to completion of the interview is ~ 16 weeks.

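### The pilot's recruitment target equals 3.2–4.2 women per site-month, but the main trial it is meant to test needs 5.2–9.0

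*Protocol article*

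**What the plan says.** In Rationale for study design, the main-trial size for the asphyxia composite is given as follows: "To detect a 30% reduction to 4.2% would require 5000 women with 80% power and 6500 women with 90% power". The next sentence is "Such recruitment may be possible using 30–40 sites over 24 months". The pilot is tied directly to that statement: "To determine whether this is feasible, the ReMIT-2 pilot trial will be conducted". Its scale is then set: it "will be conducted at approximately six sites over nine months with an aim to recruit 175–225 eligible participants during this time". Sites of different sizes are chosen to "ensure that the data are representative of the range of sites that would participate in the main trial".

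Sample size and recruitment repeats the pilot figures (nine months, about six UK sites, 175–225 participants) as an expectation. Neither section gives a rate per site, an allowance for sites opening late, or any other link between the pilot target and the main-trial configuration.

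**The concern.** Whether a definitive trial can recruit is a central question for this pilot, and the number recruited at each site is among the first feasibility outcomes listed. The pilot target and the main-trial configuration appear almost side by side, with the first presented as the test of the second. Reduced to a common unit, they do not agree. A pilot that recruits exactly as planned could be taken as encouragement for 30–40 sites over 24 months, when the same rate would leave that trial well short of its sample size.

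**Working it through.** **Inputs, all from Rationale for study design:** composite rate 6% against 4.2%; 5000 or 6500 women; 30–40 sites; 24 months. Pilot: 175–225 women, about six sites, nine months.

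**1. Do the main-trial sizes reproduce?** The article states neither alpha nor sidedness, so I assumed two-sided 5% and 1:1 allocation. The usual two-proportion formula with continuity correction gives 4908 in total at 80% power and 6496 at 90%, both within 3% of the stated figures. Without the correction it gives 4688 and 6276. The sample sizes are sound, so the mismatch lies in the sites and duration.

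**2. Pilot target per site-month.** Site-months = 6 × 9 = 54.
- 175 / 54 = 3.24
- 225 / 54 = 4.17

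**3. Main-trial requirement per site-month** = N / (sites × months).
- 5000 / (40 × 24) = 5.21
- 5000 / (30 × 24) = 6.94
- 6500 / (40 × 24) = 6.77
- 6500 / (30 × 24) = 9.03

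The text does not say which sample size goes with which number of sites. Pairing the ranges in order (5000 with 30 sites, 6500 with 40) gives 6.9 and 6.8.

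**4. Yield at the pilot's target rate over 24 months.**
- Lowest: 3.24 × 30 × 24 = 2,333 women, or 36% of 6500
- Highest: 4.17 × 40 × 24 = 4,000 women, or 80% of 5000

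For 6% against 4.2%, 2,333–4,000 women give about 51–73% power (two-sided 5%, no continuity correction).

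**5. What the pilot rate would imply for 5000 women.**
- Sites over 24 months: 5000 / (4.17 × 24) = 50 to 5000 / (3.24 × 24) = 64
- Months at 30–40 sites: 5000 / (4.17 × 40) = 30 to 5000 / (3.24 × 30) = 51

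**6. Sensitivity.**
- Five pilot sites instead of six: 175 / 45 = 3.9 to 225 / 45 = 5.0, still below 5.2.
- Recruitment dates in Trial status (12 March to end December 2018, about 9.65 months): 3.0–3.9.
- Pilot sites open on average 7 of 9 months (assumed), main-trial sites open throughout: 225 / (6 × 7) = 5.4. This passes 5.2 but not 6.8.
- The same average opening delay of d months in both trials, best case: 225 / [6(9 − d)] = 5000 / [40(24 − d)]. This gives 900 − 37.5d = 1125 − 125d, so d = 225 / 87.5 = 2.6 months. For 225 women against 6500 at 40 sites, the same equation gives 900 − 37.5d = 1462.5 − 162.5d, so d = 4.5 months.

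**The case against.** The strongest reply is that 175–225 is an aim and an expectation, and the main-trial sentence is hedged. Nothing in the article makes the target a progression criterion. The pilot will count eligible and randomised women at each site, so the true rate will be seen whatever the target was. This stands, and it limits how much harm the mismatch can do.

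A second reply is that a calendar average understates the steady rate when sites open late, and that a given delay costs a nine-month pilot proportionately more than a 24-month trial. This is also correct. However, the article states no such delay. An average of about 2.6 months in both trials closes only the single most favourable pairing (225 women; 5000 at 40 sites).

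A third reply is that the extremes (9.0 per site-month, 36%) come from pairing the larger sample with the fewest sites. That is fair, but in-order pairing still requires 6.8–6.9, well above 4.2.

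A reader might go further and infer that a pilot on target would show the main trial to be infeasible. The documents do not support that: a shortfall would count only against 30–40 sites over 24 months, and the average rate need not carry over unchanged. A reader might also fault the 5% margin on the proportion recruited for ignoring clustering by site. Any figure for that needs an assumed intraclass correlation, and the method for such intervals is commonly left to the analysis plan.

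**Conclusion.** The inconsistency is real. With all sites open throughout, the pilot target is 3.2–4.2 women per site-month against 5.2–9.0 required. Even the best case falls 20% short (4,000 of 5000 women). Meeting the target would not by itself support the stated configuration.

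This rests on about six sites, nine months, and the pilot's average rate applying to main-trial sites; the article encourages that last step by calling the sites representative. The point is worth correcting because the feasibility question depends on these numbers. It is not critical: it affects no allocation, outcome or analysis within the pilot.

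**What to change.** Reconcile the figures in Rationale for study design in one of two ways:

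- restate the main-trial sites and duration to match the pilot target (for 5000 women, about 50–64 sites over 24 months, or 30–51 months at 30–40 sites); or
- keep 30–40 sites over 24 months and state the site-opening assumption that links it to 175–225 women.

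In either case, judge pilot recruitment per open site-month against the required rate: at least 5.2 for 5000 women at 40 sites all open for the full 24 months, and more if main-trial sites are also expected to open late.

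The change is wording and arithmetic, plus site opening dates to set beside the per-site counts already planned. It needs no extra participants. The downside is that the main-trial planning figures become less favourable.
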